#### 2.8.2. Qualitative Data

The majority of the qualitative data comprises of focus group data. The way data is captured is a summary of individuals who collectively agree and discuss on the content [54]. Therefore, the first phase of analysis is to provide quantitative analysis of the subjects and the group types [55]. Focus groups can be useful to find a consensus on a phenomenon, as well as to engage with participants to discuss and share ideas that would otherwise be difficult to gather from one to one interviews [56]. In particular, the structural approach to children’s group research can be used and transferred across to adolescents so that the students’ voice to be heard [57]. Because the way a person in the focus group may consider a way to respond to the moderators’ questions could differ from what other individuals may be thinking at the time, it is important to consider the way individuals respond, with whom and in what ways [55]. Transcriptions are matched with assistant moderator notes of verbal and non-verbal behaviours. 

The data from one-to-one interviews is more straightforward. A semi-structure interview guide is used to direct the respondent to focus on the research questions and is used for further probing into these questions if the respondent needs to explain something further. Interviewees data are also merged with intonation coding to help reinforce the importance of non-verbal behaviour. The double coding from the transcription across the different qualitative approaches creates a rich source of data. 

The combination of data is inserted into NVivo software for qualitative analysis. The metadata and types of data are used to create a rich data set. The data undergoes a thematic analysis as suggested by Lederman [58] by (1) identifying the big ideas, (2) creating units of data, (3) categorizing the units, (4) negotiating categories and (5) identifying themes and use of theory. The theories surrounding social-cognitive theories, including self-efficacy theory [29], self-determination theory [31] and competence motivation theory [50] are lens used in the final steps of the content analyses. 

The data are collected through follow up measures throughout the year. The researchers incorporate verification checking at the beginning of each session to place a point where the respondents can focus on. In particular, we are interested in the processes of the intervention, as well as the potential transformation in beliefs, thoughts and actions over the course of the year. These steps are useful for designing the results in a way that allows for multi-method approach to the overall research questions. 

#### 2.8.3. Mixed Methods Analyses

Both quantitative and qualitative data can complement each other. We hope that the data that derives from both methods of inquiry can be partly explained through the literature to date and other types of data that is collected. To return to the points of evaluation of the feasibility study, there are various numbers of expected outcomes that the school is expected to achieve and they are measured directed through particular sources (Table 2). For example, the expected outcome of a broad physical education curriculum is measured through the whole school survey on participation of various physical education activities. The data taken from the beginning of the year gives insight to the types of activities that the students reported to have attended in the past 12 months. Through data collection across all year groups, the survey data can be used to determine how broad the physical education programme actually is. The post-test survey would give an indication of the extent of the physical education programme. However, reliance solely on this measure may be limited to the actual item that is included in the survey [59]. Therefore, combining the data from focus groups by the students and staff at the school can give more details about what was popular, who experienced the changes and the mechanisms in place to make the broader physical education opportunities. Therefore, the focus on the results are on the processes of creating the change, thus allowing further insight into the behavioural change techniques used to facilitate such changes. 

The SLASF log data contains both quantitative and qualitative data and can be analysed for the percent of completion towards the SLASF. Actions in relation to SLASF throughout the year form descriptive feasibility analyses. Differences in the PA audit across the year are analysed through descriptive statistics over time. In combination with the logbook of actions and the results of the PA audit more details about the feasibility of schools’ actions from the TY class can be determined in relation to desired outcomes. 

### 2.9. Availability of Data and Materials 

After completion of the study, data will be stored at the University of Limerick’s Data archive without potential identifiers and request for data can be made through the study’s principal investigator (Last author). All supplementary materials for the SLASF programme including the resource pack, template logbook and accompanying resources will be available at https://osf.io/frx6t/.

### 2.10. Ethics Approval and Consent to Participate 

The study follows the principles of the Declaration of Helsinki. The study protocol has been approved by the research ethics committee of the Faculty of Education and Health Sciences, University of Limerick (ref no. 2018/10/18_EHS). Written informed consent will be sought from participating teachers, students and students’ guardians. All participants have permission to withdraw from the study at any time and data deleted if collected. In cases of important protocol changes, requests from the ethical committee will be sought for. Trial Registration: https://osf.io/keubz/register/5771ca429ad5a1020de2872e; Registered 24th September 2018; Clinical Trial Registration: NCT03847831.

## 3. Discussion

In this year-long feasibility study of the SLASF, a mixed-method approach is used to give recommendation to stop, revise or conduct a randomised control trial. The whole-school approach requires multiple stakeholders, primarily the students in secondary level schools, the TY students, the SLASF staff and its committee, as well as the management. The theories used in this paper are based on social cognitive theories and stages of change model [29,31,50]. 

Whole-school based interventions in the promotion of PA have been increasing [11,19] although the inception of the SLASF in the secondary level schools is more complicated than primary level schools. The diversity of foci at secondary level schools brings challenges towards a uniform and national programme. This is evident to date, whereby 29% of primary schools are ASF schools, whereas less than 5% of secondary level schools have this status. Therefore, a feasibility study is needed to test the readiness prior to national roll-out. 

The results from this study would be used to help inform the development of the SLASF and report the experiences of the schools in the feasibility study. Secondary outcomes from the measures carried out in the study may lead to improved understanding of the mechanisms of the promotion of PA. Moreover, the direct mapping of the stated goals of the SLASF with measures would provide evidence. Future iterations of the SLASF may include opt in by the students to take part in the SLASF TY programme, thus providing a mixture of students who are active and inactive.

The challenges to this programme include the fidelity of the year-long programme. Schools are dynamic systems all with different characteristics based on the people who attend it. Challenging aspects could include issues arising from the coordination of the staff and pupils to carry out the tasks. There may be other activities that take place in the school, which reduce the efforts needed to run the programme or conversely, highly engagement that roles are dispersed more than previously planned. Monitoring of fidelity and carrying out process evaluations would help inform the way the programme is run.

This feasibility study is novel in design in that it a whole-school approach to the promotion of physical activity among adolescents who are empowered to organize activities over the course of the year. School management also receive an incentive by striving towards the goal and recognition of an Active School Flag. Successful piloting of the SLASF can lead to upscaling to all secondary level schools around the Republic of Ireland due to the programme endorsement by the Department of Education and Skills. Testing of the programme can be part of large scale RCT that would fit under the Healthy Ireland Demonstration Project. 

## Figures and Tables

**Figure 1 jfmk-04-00016-f001:**
[figure not shown]
Second Level Active School Flag (SLASF) Intervention and Research Components Timeline.

**Figure 2 jfmk-04-00016-f002:**
[figure not shown]
Actors of the Second Level Active school Flag.

**Table 1 jfmk-04-00016-t001:** Areas of focus for feasibility studies with measures and stopping criteria.

Focus	Measures	Stopping Criteria
Acceptability	Pragmatic survey instrument on suitability, satisfying and attractiveness for SLASF in schools for the TY and the whole-school at the end of the year.	When less than half the school students and TY consider SLASF to be suitable, satisfying or attractive to them.
	Focus group and interviews to describe the process of satisfaction of the programme, fit into the school’s culture and the positive and negative effect on the school.	When interviews describe strong statements that have a negative impact on the school’s culture or too much dissatisfaction to the programme.
Demand	PA audit of sections of the school.	No improvement over the academic year.
	Attendance list at the specific activities	Unsustainable numbers in attendance.
	Survey instrument based on readiness for PA behaviours.	Over half of students increased their readiness if they can.
	Focus groups based on the TY engagement in the SLASF process.	Discussions confirm low attendance rates and lack of demand for activities.
Implementation	Action Logs from the logbook.	Over half actions left incomplete
	Focus groups on implementation ease	Discussions where respondents report too many challenges preventing implementation
	Staff interviews	Data that suggests lack of resources to implement the programme and failures to execute the actions.
Practicality	Action plans for promotion of PA	If action plans could not be drawn up by the specified time frame
Adaptation	Registrations at events carried out as part of the action plan	Substantial decrease in participation over a 6 week period
Integration	Pre- and post-test results on PA opportunities and its participation	No increased opportunities since the beginning of the programme.
	Interviews with management about costs to organization and school policies	Descriptions whereby the costs are not sustainable. Indicators that there is a lack of staff
Expansion	Interviews of management	Descriptions of the uniqueness of the programme to the school and difficulties to roll out to other schools.
Limited Efficacy	Pre- and post-test results from the comprehensive surveys	Reduction in main outcome variables over the course of the year that is greater than the difference between each year cohort at the baseline measurements
	ASF logbook entries	Notes that report barriers to completing actions that are not manageable
	PA audit	Low level of usage when compared with the beginning of the year

**Table 2 jfmk-04-00016-t002:** Aligning outcomes with measures.

SLASF Target Areas	Measures of Efficacy	Details
Physically educated	Self-efficacy in PA	Student survey
Physically active school community	Comprehensive Survey and focus groups	Survey item and discussions
Broad physical education	Whole-school survey and focus groups	List of physical education activities and discussions
Balanced physical education	Teacher scheme of work	Teacher records
More inclusiveness	Teacher scheme of work	Teacher records
Partnership with others to promote pa culture	TY logbook	Taster session from ASW
Active school week	TY logbook	Record of entries
Increased concentration	Harter scale	Student survey
Improved learning	Teachers perceptions	Student and teacher survey
Maintenance of discipline	Teacher records	Discipline records
Improved test results	Winter and summer test	Academic records
School enjoyment	Questionnaire	Student survey
Increase Daily PA	Accelerometers	Comprehensive Data
Reduced sitting time	Accelerometers	Comprehensive Data
Reduction in overweight and obesity	Self-report and anthropometric measures of height and weight	Comprehensive data

**Table 3 jfmk-04-00016-t003:** Battery of questionnaires.

Battery	Items	Response Scales	Psychometric Information
PA Screening measure	2 items on number of days in a week of at least 60 min of MVPA per day	0–7 days	Validity & Reliability [5,44]
PA opportunities	Modified items about local opportunities for PA to the context of schools instead of ‘residential area’	5 point scale, 1 = disagree a lot, 5 = agree a lot	Original items used from an interview guide.
The exercise self-efficacy scale for adolescents	10 items on confidence to participate in a variety of conditions	11 point sliding scale, 0 = not at all confident, 10 = very confident	Nigg & Courneya, 1999 [45]
PA peer support scale	4 items on the frequency of peers influence for PA	0 = never, 5 = every day	Prochaska et al., 2002 [46]
PA, plans, expectancy and intention	Modified 3 items on the planning, expectancy and intention to do PA in the coming week	1 = unlikely, 8 = likely	Hagger et al., 2001 [47]
Readiness for behaviour change	Single item to determine which stage of the transtheoretical model in terms of PA	Select one item of each stage of the transtheoretical model	Lee et al., 2001 [48]
Perceived school performance	Single item about perceptions of teacher’s evaluation of students’ grade	Very good, good, average, below average	Felder-Puig et al., 2012 [49]
Perceived school performance	Two items about the students perception of their school grades	5 point scale, 1 = strongly disagree, 5 = strongly agree	Felder-Puig et al., 2012 [49]
Harter’s Self-perception scale for adolescents	5 items from the scholastic competence subscale.	Polarised responding	Harter et al., 1982 [50]
Belonging in school	2 items on belonging to a school	1 = Strongly agree, 5 = strongly disagree	OECD
School satisfaction	How do you feel about school a present	1 = I like it a lot, 5 = I don’t like it at all	HBSC since 2001
School effort	How pressured do you feel by the schoolwork you have to do	Not at all A little, Some, A lot	HBSC since 2001
Participation of organised activities	3 items about the student-led activities at school.	1 = Strongly agree, 5 = strongly disagree	HBSC in 2013/14
Kidscreen-27	Items on the physical and psychological well-being and the autonomy and parent relations	Not at all, Slightly, Moderately, Extremely	Ravens-Sieberer, et al., 2006 [51]

**Table 4 jfmk-04-00016-t004:** Sample size descriptions.

School	Students	Girls	Boys	Teachers	DEIS	Comprehensive (N)
Intervention						
A	971	971	-	70	N	100
B	863	440	423	70	N	150
C	1313	664	649	120	Y	150
Control						
D	582	582	-	41	N	123
E	629	322	307	45	N	121
F	378	206	172	35	Y	88

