### 2.2. Recruitment

#### 2.2.1. School Recruitment

The SLASF programme is a comprehensive programme and employs a whole school approach. As an intervention programme, schools were invited to take part if they are not currently in the process of obtaining the Active School Flag. The normal process of the SLASF recruitment is for schools to make an application but this was suspended to allow time to develop the new model. Schools that were interested in carrying out the feasibility study contacted the Active Schools office and requested to pilot the second level programme. There were three schools that responded and accepted because they each have a strong well-being structure in place in their schools. This is a feasibility study with secondary outcomes on efficacy hence matched control schools (one girls only, one mixed and one mixed DEIS school) were recruited to take part in the survey component of the study. No reserve list was formed for this cohort but engagement of all three schools throughout the year to follow the feasibility and evaluate the SLASF process.

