### 2.8. Data Analyses

#### 2.8.1. Quantitative Data

The data from the surveys are analysed through relevant statistical methods for the follow up data in this feasibility study. Compatible data between comprehensive and basic surveys can be used to determine the test-retest reliability of the items given that a smaller subsample of the entire school. As reliability is an important psychometric property for question items, this is carried out during the first phase of data collection. 

Students take part in the comprehensive study have their measures taken two times during the academic year. The first time takes place in autumn 2018 and the second takes place six months later during the spring 2019. Accelerometer data are transferred through the ActivPal software based on 15sec epoch. The standardised cut-offs for different types of motion; sleep, standing, light, moderate and vigorous PA are then compared at an individual level from pre- and post-test time points. Similarly, the height, weight and grip strength data is compared between the time points and used to control the differences in accelerometer data. Comprehensive survey data is also analysed with differences in PA and school related factors. 

Exploratory approaches include cross-sectional multivariate analyses of PA and school-related factors as independent variables and device-based PA and perceptions of PA opportunities as the dependent variables. Mixed models and multi-level regression analyses can be used on the data that has sufficient follow up data from the first time point. The multi-level approach takes into account between- and within- individual processes that explain variances in the outcome measures. Through this approach, it is possible to test the extent of PA (psychosocial variables) and school-related factors in relation to changes in PA levels and opportunities, at the same time to examine the individual versus the school factors that contribute to the outcome variables. 

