The follow-up data adds another level of analysis that can test the changes through the intervention. It makes it possible to examine, for example, the changes in PA levels across the schools from the beginning and the end of the study, while also taking into account changes in the psychosocial variables included in this study. The interactions between the contexts can confirm behavioural change theories by examining the mediating and moderation mechanisms in PA levels. The majority of the statistical analysis would be carried out using IBM SPSS. 

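### The limited-efficacy stopping rule sets an uncontrolled six-month change against a one-year gap between cohorts and states no comparison with the control schools recruited for efficacy

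*Protocol article*

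**What the plan says.** Table 1 lists the criteria that feed the decision to stop, revise or go on to a randomised trial. Section 1.3 says such rules must be fixed before the analysis. For Limited Efficacy, the first measure is "Pre- and post-test results from the comprehensive surveys" and the criterion is "Reduction in main outcome variables over the course of the year that is greater than the difference between each year cohort", with the gap taken at baseline. The row names no outcome, no particular cohort gap and no control comparison.

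On timing, section 2.8.1 says of the comprehensive measures: "The first time takes place in autumn 2018 and the second takes place six months later during the spring 2019". Section 2.5.4 makes the comprehensive survey one of the stations at those visits, so the six-month spacing applies to the survey outcomes. The abstract instead places data collection at the start and finish of the school year, and the Table 1 row speaks of the year as a whole.

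On controls, section 2.2.1 says: "This is a feasibility study with secondary outcomes on efficacy hence matched control schools" were recruited, and that they join the survey part of the study. Table 4 gives their comprehensive numbers. Section 2.8.1 describes pre-post comparisons, mixed and multi-level models, and an examination of "the changes in PA levels across the schools from the beginning and the end of the study". It does not mention the control schools.

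**The concern.** A pre-post change contains at least three things: natural decline with age, season, and any effect of the programme. The rule allows for the first by borrowing the cross-sectional gap between year groups. That gap covers a longer span than the change it is compared with. The second is not allowed for at all, since one survey falls in autumn and the other in spring. A group measured over the same months would remove both. Such a group was recruited for this purpose, but the rule as written does not call on it.

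At stake is the only quantitative efficacy criterion drawn from the comprehensive surveys. It could stay silent while pupils decline faster than their peers. It could also be triggered, or held back, by season alone.

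**Working it through.** **Inputs.**
- Interval between surveys: six months (section 2.8.1). Nine months is my assumption for a reading as a full school year.
- Spacing of neighbouring cohorts: about twelve months, since one class is drawn from each year group (section 2.2.2).
- Natural decline (section 1): a pooled mean of 7% per year; and, from the national study, 18% meeting the guideline at age 12 against 6% at age 18.
- Comprehensive numbers (Table 4): intervention 100 + 150 + 150 = 400; control 123 + 121 + 88 = 332.

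The plan states no power, alpha or margin, so there is no planned figure to reproduce.

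**Step 1: expected change against threshold.** Pooled figure, compounded: expected fall over t years = 1 − 0.93^t.
- One-year cohort gap (the threshold): 7%.
- Six months: 1 − 0.93^0.5 = 3.6%; ratio 7 / 3.56 = 1.96.
- Nine months: 1 − 0.93^0.75 = 5.3%; ratio 7 / 5.30 = 1.32.

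National figures, linear: (18 − 6) / 6 = 2.0 percentage points per year.
- Six months: 1.0 point; ratio 2.0.
- Nine months: 1.5 points; ratio 1.33.

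Both sources give a tolerance of about 2 times the expected fall at six months and about 1.3 times at nine.

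**Step 2: what the rule responds to.** Let d be the annual natural decline, t the interval in years, s the autumn-to-spring seasonal shift and p the programme effect (both positive if favourable).
- Observed change = s − d·t + p.
- The rule triggers when the fall exceeds d, that is, when s + p < −d(1 − t).
- At t = 0.5 this is s + p < −d/2.

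Season and programme enter only as a sum, so the rule cannot distinguish them. A favourable seasonal shift hides an equal amount of harm, and an unfavourable one can trigger the rule with no programme effect.

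**Step 3: what a concurrent comparison does.**
- Change in control schools over the same months = s − d·t.
- Intervention change minus control change = p, if season and ageing act alike in both groups.

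The 332 control pupils would supply this contrast. Neither the Table 1 row nor section 2.8.1 states it.

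**The case against.** **A stopping tolerance may be lenient.** In a pilot it need not equal the expected decline. That stands. But a lenient margin should be chosen and stated. Here the leniency is a by-product of setting six months against twelve, and it moves from about 2 times to about 1.3 times depending on which timing statement is followed.

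**Section 2.8.1 does not exclude the control schools.** It plans multi-level models and looks at change across schools, and an article may leave the exact contrast to a fuller plan. That is fair for the models. It does not rescue the stopping rule, which is stated in full and is purely pre-post.

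**Ageing is partly handled.** The cohort gap is itself a rough ageing allowance, so it would be wrong to say that age is ignored. Only season is wholly uncorrected.

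**A reader might infer that the rule counts improvement as harm,** because some Table 3 items run the other way. School satisfaction, for example, is coded "1 = I like it a lot", and the belonging and organised-activity items put strong agreement at 1. The documents do not support that inference. They do not say that raw scores are used or that these items are main outcomes. The activity, self-efficacy, peer-support and intention scales run upwards, and a reduction can be read as a worsening. What can be said is that the main outcome variables are undefined while Table 3 mixes scoring directions.

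**A reader might also infer that sampling noise makes the threshold worthless.** That depends on choices the documents do not make. Assume a yes/no outcome at 12% and 67 pupils in each of six year groups, without clustering. One adjacent gap then has a standard error of sqrt(2 × 0.12 × 0.88 / 67) = 5.6 points. A linear slope over the six groups has sqrt(0.12 × 0.88 / 67) / sqrt(17.5) = 0.95 points. The supportable point is that the rule does not say which gap it means.

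**Conclusion.** The concern holds in this form: the rule compares an uncontrolled autumn-to-spring change with a cross-sectional gap spanning a longer period, and it makes no stated use of the schools recruited to support the efficacy outcomes. The tolerated decline is about twice the expected one on the six-month interval of section 2.8.1, and about 1.3 times on an assumed nine months. This rests on the article's own decline figures and on neighbouring cohorts being a school year apart. The finding that season is inseparable from programme effect needs no figures.

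This should be fixed, but it does not threaten the study. The row is one of 17 criteria in Table 1, the primary objective is acceptability, efficacy is secondary, and nothing says this row decides the outcome alone.

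**What to change.** 1. Reconcile the interval wording between the Table 1 row, the abstract and section 2.8.1.
2. Name one or two survey outcomes for the rule and state that they are coded so that higher is better.
3. Restate the rule: the baseline-adjusted change in the intervention schools, minus the change over the same months in the control schools, is unfavourable by more than a pre-stated margin. Report it with a confidence interval that allows for clustering by school.
4. Choose the margin deliberately. Simply asking for a result worse than control would trigger about half the time with no true effect. One option is the baseline year-group slope, pooled over all cohorts and pro-rated to the actual interval. On the 7% figure that is about 3.6% at six months, close to the excess of 7 − 3.6 = 3.4% that the present rule allows when season plays no part. At nine months it is 5.3%, against a present excess of 7 − 5.3 = 1.7%. The gain from the change is therefore the removal of season and shared ageing, not automatic strictness.
5. Use the same group-by-time contrast in section 2.8.1 for the survey outcomes. Label the accelerometer pre-post change as descriptive if the controls provide survey data only.

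**Cost.** Changes to Table 1 and the analysis text. No new data are needed, provided the control pupils complete the comprehensive survey at both time points, which the article implies but does not spell out. With three non-randomised schools per arm the interval will be wide, and residual confounding between schools remains.

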In addition, all students in the selected year group in the school will take part in a four weeks PA module delivered by the Social and Personal Health Education (SPHE) teachers. There would have to be a ‘Did You Know?’ campaign around the school that helps raise awareness about the benefits of PA for teenagers, in particular the positive impact that PA has upon focus, concentration and academic achievement. Another practical task for the SLASF team is to signpost an Active School WALKWAY. The walkway is a route that can be used by the students in the school during recess time or under teacher supervision for active learning activities, before/after tests or during free classes. SLASF, in partnership with Get Ireland Walking, designed Active School WALKWAY packs consisting of colourful outdoor all-weather sign post plaques which include orienteering symbols. One of the tasks that the SLASF TY class have to undertake is to map, measure and erect the walkway signposts to create a school walking route. A school WALKWAY Day where all classes get the opportunity to complete the walkway route with their teachers on a nominated school day needs to be agreed by school management. Then it is organised and promoted by the SLASF TY team. The organised walkway can be used as part of orienteering activities during timetabled physical education, as well as other school-based initiatives. 

As the year ends, the school prepares for the accreditation visit for the certificate. A follow up visit takes place during the acquisition of the flag year. Prior to this, the school needs to organise a community mapping exercise and community events which should help with the design of the Active School Week (ASW) programme. The main aims of the ASW are to promote PA in a fun and inclusive way, as well as raising awareness about the availability and variety of PA opportunities for teenagers and their families in their local community. Throughout this week the school provides many and varied opportunities for staff and students to become more physically active throughout the school day.

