#### 2.5.3. Expected Outcomes Tables and Measures

According to their training resources, the programme aims to impact on a number of areas. However, to measure them all, multiple sources are required. A collection of survey instruments can be used to measure some of the outcomes, whereas some interviews can be used to evaluate other outcomes. In addition, the programme is year-long and a whole-school approach, hence site visits and checking on progress through logbook entries would be used to determine the processes carried out during the study. In Table 2, there is a list of the areas that SLASF aims to promote and some measures that can be used to test these outcomes.

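### Table 2 gives concentration one efficacy measure, a scholastic-competence subscale, and no listed instrument is described as measuring concentration

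*Protocol article*

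**What the plan says.** Section 2.5.3 introduces Table 2 as a list of the areas the programme aims to promote, with "some measures that can be used to test these outcomes". The table has 15 target areas, a column for measures of efficacy and a column for details. In the row "Increased concentration", the measure is a self-perception scale and the detail is the student survey. No second source is given.

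Table 3 describes the questionnaire battery. Its one matching entry is "Harter’s Self-perception scale for adolescents", and the items column reads "5 items from the scholastic competence subscale".

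Two later places rely on the mapping. Section 2.8.3 says that the outcomes expected of the school are measured through the sources in Table 2. The Discussion says that "the direct mapping of the stated goals of the SLASF with measures would provide evidence".

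**The concern.** The target and its measure carry the names of different constructs. A scholastic competence subscale of a self-perception instrument records a student's view of his or her own academic ability. Concentration is a matter of attention, and either can change without the other.

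The error could run both ways. If students come to feel more able at school for reasons unrelated to attention, the mapping invites the conclusion that concentration improved. If concentration improves but self-rated ability does not move, the mapping invites the opposite conclusion. Better precision or a comparison group would not help, because both act on the same score.

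The programme itself promotes this benefit. Section 2.5.2 describes a school campaign on "the positive impact that PA has upon focus, concentration and academic achievement". A result reported under the concentration label could therefore feed back into the programme's own message.

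**Working it through.** No formula applies and the protocol gives no figure to reproduce. The check sets the tables and text side by side.

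1. **Target to measure (Table 2).** The concentration row has one measure, the self-perception scale, taken from the student survey. Two other rows, on the physically active school community and on broad physical education, name focus groups as a second source. This row does not.

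2. **Measure to content (Table 3).** The battery has one such scale, and only five items from one subscale are used. The subscale's label refers to scholastic competence. Section 2.8.2 cites the same reference for competence motivation theory, which agrees with that reading.

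3. **Search for another measure.** Table 3 has 14 rows:
   - Six concern physical activity: screening, opportunities, self-efficacy, peer support, plans and intention, and readiness.
   - Two concern perceived school performance.
   - One is the self-perception subscale.
   - Four concern belonging, school satisfaction, schoolwork pressure and organised activities.
   - One is a well-being instrument, described as covering physical and psychological well-being, autonomy and parent relations.

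   The sum is 6 + 2 + 1 + 4 + 1 = 14, and the number described as measuring concentration or attention is 0. The basic survey (Sections 2.5.4 and 2.6.2) concerns participation in and barriers to physical activity, and the later whole-school surveys concern process evaluation.

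4. **Could scholastic competence be the protocol's own word for concentration?** The text argues against it. Section 2.5.2 names concentration and academic achievement as separate benefits, and Table 2 gives improved learning and improved test results their own rows with their own sources.

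5. **Would the comparison group rescue the inference?** Section 2.2.1 adds matched control schools for the survey. Table 4 expects 100 + 150 + 150 = 400 comprehensive participants in intervention schools and 123 + 121 + 88 = 332 in control schools. That allows a comparison of perceived competence between groups, but it does not make the score a measure of concentration.

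**Result:** one target, one assigned measure, and that measure is labelled as another construct. Nothing elsewhere in the document supplies a replacement.

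**The case against.** Four points can be made for the plan.

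- **The mapping is permissive and the aim is secondary.** Section 2.5.3 says the measures can be used, the study is about feasibility, and no hypothesis or named analysis on concentration is stated. The limited-efficacy stopping criterion in Table 1 does not name concentration either. This stands. It would be too strong to infer that the study will report an effect on concentration; the documents show only that the mapping permits that reading.

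- **The five items are not printed.** This also stands. The judgement rests on the subscale's name and on how the protocol uses its reference. The document shows that no measure is described as concentration. It does not show that the items have been proved invalid for it, nor does this check establish that the other 14 targets are well measured.

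- **The authors know that survey items have limits.** Section 2.8.3 warns, in its physical-education example, against relying on the survey item alone and brings in focus groups. That shows awareness, but it is not carried over to the concentration row.

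- **A similar fault might be inferred in Table 3, but is not established.** The row labelled as school effort asks "How pressured do you feel by the schoolwork you have to do", so a reader might infer that greater pressure would be scored as greater effort. The documents do not support this. The row is not mapped to any target in Table 2, no numeric coding or direction is given for it, and the printed question shows what is being asked. What remains is a loose label, and scoring direction is commonly left to an analysis plan.

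**Conclusion.** The point holds in limited form. One of the 15 targets in Table 2 is paired with a subscale named for a different construct, and no listed instrument is described as filling the gap. Because the protocol treats the mapping as its evidence on the programme's goals, a change in perceived scholastic competence could be read as a change in concentration.

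The consequence is small. It touches a secondary efficacy aim, leaves the acceptability objective in Section 1.4 as it is, and gives no number to correct. The conclusion assumes that the subscale's content matches its label and that Tables 2 and 3 list the measures in full.

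**What to change.** In Table 2, keep "Increased concentration" as a target area, because Section 2.5.3 attributes these aims to the programme's own training resources. Renaming the row to fit the questionnaire would hide that a programme aim is unmeasured. Change the measure column instead: remove the self-perception subscale and state that concentration is not measured quantitatively and will be addressed only through the focus groups and interviews already planned. Report the five items under their own name, perceived scholastic competence.

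The cost is a wording change in one table row and a matching line in the reporting. The topics that Table 1 lists for focus groups and interviews do not name concentration, so a prompt would probably have to be added to the guides. The downside is that one secondary programme aim can no longer be claimed quantitatively. What students and staff say about it would be evidence of perception, not of a measured increase.
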